### Eligibility criteria

2.3

Recruitment sites have been selected based on the following criteria:

They are either approved outpatient departments of clinics for child and adolescent psychiatry and psychotherapy,Medical care centers for child and adolescent psychiatry and psychotherapy, orPractices for child and adolescent psychiatry and/or psychotherapy listed with the local Association of Statutory Health Insurance Physicians or Chamber of Psychotherapists.Local healthcare providing professionals need to be experienced with child and adolescent psychiatry and/or psychotherapy. They will comprise specialists for child and adolescent psychiatry, registrars in training as child and adolescent psychiatrists, psychologists, certified psychotherapists for children and adolescents, or psychotherapists for children and adolescents in training.All sites will be supervised by a certified experienced child and adolescent psychiatrist and/or psychotherapists.The sites are located in Germany.

Participants will be included in the study if they:

Are between 10 and 19 years old (WHO definition of adolescence);Reach the cutoff values for hazardous or pathological use on the Gaming Disorder, Social Media Use Disorder or Streaming Disorder Scale for Adolescents or Parents (GADIS-A/-P, SOMEDIS-A/-P, STREDIS-A/P);Fulfill the ICD-11 criteria of disordered or hazardous gaming, social media use, or streaming based on clinical examination;Have sufficient German language skills;Give written informed consent (for adolescents <16 years with additional informed consent of legal guardians).

OR

Are a parent, i.e., caregiver, of a patient fulfilling the criteria above.

Participants will be excluded from the study if they:

Show symptoms of an acute psychosis;Are acute suicidal;Are substance intoxicated or fulfill criteria of substance use disorder (alcohol, illegal substances, and non-prescribed medication);Show a severe reduction in literacy and/or intelligence;Have no access to the Internet or are not able to operate on a smartphone, tablet, or computer.

### Sample size calculation

2.4

The sample size was computed with the procedure tests for Two Means in a Cluster-Randomized Design in PASS 16.0.4 (NCSS, LLC. Kaysville, Utah, United States). A small standardized mean difference (Cohen’s *d* = 0.2) between IG and CG in symptom reduction measured as change from baseline to post-intervention is assumed. The number of study centers is assumed to be 50, each recruiting 27 patients on average. This leads to a feasible sample size of 667 per group. The coefficient of variation of the cluster sizes is set to 0.4 because recruitment is assumed to be heterogeneous due to the different sizes of the study sites. The intra-cluster correlation (ICC) is set to 0.005. With the achievable sample size of 667 patients with respective parents in each of the two groups (*N*_dyads_ = 667) and a two-sided type I error of 5%, the power will be 77%. A dropout rate of 40% before post-intervention assessment (10 weeks) and 20% before follow-up (20 weeks) is assumed. The sample size calculation refers to the three primary hypotheses, taking into account the hierarchical structure. A drop-out rate of 40% before post-intervention assessment (week 10) is considered. With an estimated proportion of adolescents in the outpatient setting with hazardous or disordered digital media use of 20% and a participation rate of 50%, *N* = 13,340 patients must be initially screened. Due to the novelty of the study, conservative estimates were chosen for the assumed effect size and drop-out and participation rates. Digital CBT-based intervention studies with comparable adolescent age groups reported small to medium effect sizes regarding the reduction in depression and anxiety symptoms (36, 37).

Three nuisance parameters (drop-out rate, coefficient of variation, and intraclass correlation coefficient) enter the sample size planning, the assumptions of which are not known with certainty. Therefore, a blinded interim analysis will be performed after the collection of post-intervention data from half of the planned patients (200 per group, 400 total) to estimate the nuisance parameters and possibly adjust the sample size.

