**Methods:**

Res@t digital (Resource-Strengthening Training for Adolescents with Problematic Digital-Media Use and their Parents) is the app-based translation of the first model-based digital intervention for adolescents with DMUD and their parents based on CBT. It comprises separate but content-related modules for adolescents (Res@t–A) and parents (Res@t–P), applying multimodal techniques. The effectiveness of Res@t will be evaluated within a multicenter cluster-randomized controlled evaluator-blinded pre–post follow-up trial with the waitlist control group (CG). In addition to the Res@t program in the intervention group, both groups will receive treatment as usual within primary child and adolescent psychiatric/psychotherapeutic healthcare. The primary outcome addresses DMUD symptom reduction after 10 weeks. Secondary outcomes are related to a reduction in psychological and family-related problems and an increase in parental self-efficacy. All outcomes will be assessed using standardized self-report measures. A total of 1,334 participating adolescent–parent dyads from a large clinical network throughout Germany are planned to be included in the primary analyses based on an intention-to-treat approach, applying linear mixed models.

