### Data analysis

2.12

Data will be analyzed by the independent statisticians at the IMBE with sophisticated experience in multicenter therapy studies. Descriptive statistics will be presented with respect to both the entire sample and group-wise. The primary analysis is based on the intention-to-treat (ITT) approach with all randomized patients. The significance level will be set at 5% (two-sided). All three primary hypotheses are structured hierarchically. The second primary hypothesis will only be evaluated in a confirmatory way if the first primary hypothesis leads to a significant test result. The third primary hypothesis will only be evaluated in a confirmatory way if the second primary hypothesis leads to a significant test result. For the analysis of each primary hypothesis, a linear mixed model with implicit maximum likelihood correction of missing values under the missing-at-random assumption will be calculated, respectively. The change in DMUD symptoms from baseline to post-treatment will be used as an outcome variable, randomization group, type of DMUD (social media, gaming, streaming), recruitment site size and location as fixed effects, individual recruitment site and patient nested within site as random effects, and the baseline DMUD score as a covariate. The interaction between the randomization group and media usage pattern (hazardous vs. pathological) as well as effects of incomplete dyads will be tested within secondary analyses.

To examine the impact of missing values on the outcome of the primary analysis, sensitivity analyses will be performed using multiple imputation methods to replace missing values. The primary endpoint at follow-up and the secondary endpoints will be investigated exploratorily using analogous methods, which are adequate for the scale type. The following subgroup analyses are planned: severity of DMUD, sex, education, and socioeconomic status. Qualitative assessments of treatment provider satisfaction will be supplemented. Details of the analysis will be specified in a statistical analysis plan. The analysis will be performed with the latest version of the software package R (70).

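### The 77% power is that of the first primary hypothesis alone, on about 400 analysed per group; it is not the power to confirm the second or third hypothesis in the fixed sequence

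*Protocol article*

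**What the plan says.** Section 2.4 (Sample size calculation) assumes "A small standardized mean difference (Cohen’s *d* = 0.2) between IG and CG in symptom reduction", 50 sites recruiting 27 patients each on average, a coefficient of variation of cluster size of 0.4 and an ICC of 0.005. It then attaches the power to the recruited number: "With the achievable sample size of 667 patients with respective parents in each of the two groups" "and a two-sided type I error of 5%, the power will be 77" per cent. The same section assumes 40% dropout before the week-10 assessment. It puts half of the planned patients with post-intervention data at 200 per group, so 400 per group are planned.

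On the scope of the calculation, 2.4 says: "The sample size calculation refers to the three primary hypotheses, taking into account the hierarchical structure". No other power figure is given, and no correlation between the adolescent, parent and clinician ratings.

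Section 2.12 (Data analysis) sets a fixed sequence at the two-sided 5% level: "The second primary hypothesis will only be evaluated in a confirmatory way if the first primary hypothesis leads to a significant test result". The same condition links the third hypothesis to the second. The abstract says that 1,334 dyads "are planned to be included in the primary analyses based on an intention-to-treat approach".

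**The concern.** In a fixed sequence, a single power figure can describe only the first step, unless it is explicitly a joint probability. Confirming hypothesis 2 requires tests 1 and 2 both to succeed, and confirming hypothesis 3 requires all three. Unless the test statistics are perfectly correlated, those probabilities are below the power of the first test. A statement that the calculation refers to all three hypotheses with the hierarchy accounted for, placed beside one figure, leaves open what the 77% covers.

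Parent- and clinician-rated effects are confirmatory aims of the trial. A sponsor or reader judging whether the sample supports them needs the power of those steps. The planned blinded interim analysis may also adjust the sample size, so what the 77% refers to should be settled before then.

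**Working it through.** **Inputs from section 2.4.** d = 0.2; two-sided alpha 5%; 50 sites, taken as 25 per group; ICC 0.005; coefficient of variation (CV) 0.4; 667 recruited per group; 40% dropout before week 10.

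**Input not in the document.** The correlation between the three test statistics. Section 2.10.1 says only that self- and parent ratings agreed moderately. That describes validation samples, not the correlation of treatment-effect statistics, and it does not concern clinicians. I assume a common correlation and show the range 0 to 0.9.

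**Step 1: reproduce the stated figure.**

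- Analysed per group: 667 × 0.6 = 400, or 400/25 = 16 per site.
- Design effect: 1 + ((1 + CV²)m − 1) × ICC = 1 + (1.16 × 16 − 1) × 0.005 = 1.0878.
- Effective n per group: 400/1.0878 = 367.7.
- Noncentrality: 0.2 × √(367.7/2) = 2.712.
- Power of one two-sided 5% test: 77.4% by the normal approximation, 75.7% by a t test with 48 cluster degrees of freedom.

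The stated 77% is reproduced as the power of a single test on 400 per group.

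**Step 2: the same formula with 667 analysed.** m = 26.68, design effect 1.150, effective n 580, noncentrality 3.406. Power is 92.6% (91.6% with cluster degrees of freedom). So 667 is the recruited number behind the 77%, not the analysed number.

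**Step 3: power along the sequence.** Assume that each rater's test has d = 0.2 and 400 analysed per group. Each statistic is then normal with mean 2.712 and variance 1. The probability of confirming a step is the multivariate normal probability that every statistic up to that step exceeds 1.96.

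| Assumed correlation | H1 | H1 and H2 | All three |
|---|---|---|---|
| 0 | 77% | 60% | 46% |
| 0.3 | 77% | 63% | 53% |
| 0.5 | 77% | 65% | 57% |
| 0.7 | 77% | 68% | 62% |
| 0.9 | 77% | 72% | 69% |

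The first row can be checked by hand: 0.774² = 0.599 and 0.774³ = 0.464. Only a correlation of 1 brings all three back to 77%.

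**Step 4: failure after a successful first test.** Conditional on success on hypothesis 1, failure at step 2 or 3 has probability 1 − P(all three)/P(H1). That is 1 − 0.527/0.774 = 32% at correlation 0.3, and 1 − 0.623/0.774 = 20% at correlation 0.7.

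**The case against.** **The sentence may be about alpha only.** It can be read as saying that a fixed sequence needs no alpha split, so each test is planned at the full 5%. That is correct for type I error, and the fix should keep it. It does not turn 77% into the power of steps 2 and 3.

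**Joint power is not required.** The hypotheses are ordered, not co-primary, and the first can be confirmed alone. Powering the first step is a common choice. This stands: the design need not change. The point concerns what the figure is said to cover.

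**77% can be reached another way.** With 667 analysed per group and cluster degrees of freedom, three independent tests give 0.916³ = 0.77. This would be a joint figure, but it leaves out the 40% dropout that 2.4 says is considered. It also conflicts with an interim analysis at 200 per group as half of those planned. On neither route does 77% cover both the dropout and all three hypotheses.

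**Stronger readings that the document does not support.**

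- A reader might infer that 667 against 400 is an arithmetic error. It is not: 2.4 states the dropout, and the interim numbers imply 400. The wording is ambiguous, no more.
- A reader might infer that the abstract's 1,334 is wrong. Section 2.12 defines the primary analysis as intention-to-treat on all randomised patients, with likelihood-based handling of missing values, so 1,334 can be the analysis set. It is just not the number expected to have week-10 scores.
- A reader might infer that the protocol promises 77% power for each of three claims. It does not say so; it gives one figure and a loose statement of scope.
- A reader might infer that failing on the parent or clinician rating is likely even if the intervention works as assumed. Step 4 does not bear that out: after success on hypothesis 1, the chance is about 20% to 32% for correlations of 0.7 to 0.3.
- A reader might add further loss of parent scores, because incomplete dyads are foreseen. The document gives no rate and counts dyads in its sample size, so the 40% may already cover them.

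**Conclusion.** The point holds as a misdescription of a power figure that is itself calculated correctly. The 77% is the power of one two-sided 5% test, the first primary hypothesis, with about 400 analysed of 667 recruited per group. It is not the probability of confirming the second or third hypothesis, although 2.4 says that the calculation refers to all three with the hierarchy accounted for.

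The shortfall depends on a correlation that the document does not give. Over 0 to 0.9 the probability is about 60% to 72% for hypotheses 1 and 2 and about 46% to 69% for all three. These figures assume d = 0.2 and 400 analysed per group for every rater; a smaller effect or sparser data for parents or clinicians would lower them. That the later steps have less than 77% follows from the testing order under these assumptions at any correlation below 1. The size of the gap is illustrative, and no single correlation should be singled out.

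The correction should be made: it costs little, and the figure is the trial's only statement of power.

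**What to change.** In section 2.4:

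1. State that 77% is the power for the first primary hypothesis, with about 400 analysed of 667 recruited per group after 40% dropout.
2. Replace the hierarchy sentence with one saying that the fixed sequence needs no alpha split, so each test is at two-sided 5%, but that the power to confirm hypotheses 2 and 3 is lower.
3. Give that power as a range, labelled as resting on assumed correlations of the test statistics: with d = 0.2 and 400 analysed per group for every rater and correlation 0 to 0.9, about 60% to 72% for hypotheses 1 and 2 and about 46% to 69% for all three.

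In the abstract, as a clarification only: say that 1,334 dyads are to be enrolled, of whom about 800 (1,334 × 0.6) are expected to have week-10 data.

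The cost is a few sentences. No patients are added, and neither the design nor the testing order changes. The stated prospects for hypotheses 2 and 3 become less favourable.

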### Randomization

2.5

A stratified cluster randomization will be employed, resulting in each recruitment site (outpatient department or practice) being randomly allocated to the intervention or waitlist control. Stratification is performed according to recruitment site size (annual patient number ≤ 600, > 600 and ≤ 1,600, and > 1,600) and location (urban or rural). An independent statistician at the Institute of Medical Biometry and Epidemiology (IMBE) at the University Medicine Hamburg-Eppendorf will randomly allocate recruitment sites using computerized random number generations within each stratum to IG or CG based on internal standard operating procedures, without knowledge of the identity of recruitment sites (with variable block length). Cluster randomization will be applied to avoid contamination between IG and CG conditions regarding TAU. Based on the resulting allocation, the intervention will be made available immediately (IG) or after the recruitment phase and follow-up data collection is completed (CG).

### Assessment and data collection

2.6

Clinical assessments with the adolescents and respective parents will be realized at screening, baseline, week 10 (post-intervention), and week 20 (follow-up). By the latter, the durability of the treatment effect should be estimated. Screening and baseline visits should not be apart by more than 4 weeks, otherwise a clinical reevaluation will become necessary. In addition to clinical diagnosis and post-treatment evaluation, all assessments are performed digitally via standardized questionnaires, which are provided on an online platform without the involvement of the clinician. They will be automatically presented to the participants at the time points according to the study protocol. Participants will receive e-mail reminders just before and during the scheduled time frame. All data will be initially stored in a patient dossier on the ISO-certified e-mental health platform run by Embloom^1^ before pseudonymization and secure transfer to the central study center. Regular visits with the clinician will take place within TAU. These should support compliance and adherence to keep the drop-out rate as low as possible. Figure 1 shows all study phases including assessment time points. Table 1 shows all questionnaires and items used in the current study. Table 2 shows the schedule of the questionnaire application.

**Figure 1 fig1:**
[figure not shown]
Flow chart of the study. ^1^Total number of adolescent–parent dyads; ^2^Participants of the waitlist control group will be offered the Res@t intervention after data collection is completed. DMUD, digital-media use disorders; TAU, treatment as usual; IG, intervention group; CG, control group.

**Table 1 tab1:** Overview of study questionnaires for adolescents and their parents.

	Instrument	Construct	Number of items	References
*Adolescents*				
	Sociodemographics	Sociodemographic data including age, sex, and educational status	18 Items	Standard, adapted to setting
	Media use	Media use (duration and frequency)	13 Items	(38)
	Gaming Disorder Scale for Adolescents (GADIS-A)	Gaming disorder according to ICD-11 criteria	10 Items	(39)
	Social Media Disorder Scale for Adolescents (SOMEDIS-A)	Social media disorder according to ICD-11 criteria	10 Items	(40)
	Streaming Disorder Scale for Adolescents (STREDIS-A)	Streaming disorder according to ICD-11 criteria	10 Items	(15)
	Strength and Difficulties Questionnaire (SDQ)	Emotional and behavioral problems in children and adolescents (self-report)	25 Items	(39, 41, 42)
	Pittsburgh Sleep Quality Index (PSQI)	Sleep quality	24 Items	(43)
	Epworth Sleepiness Scale - Children and Adolescents (ESS-CHAD)	Day-time sleepiness	8 Items	(44–46)
	Perceived Stress Scale (PSS-10)	Psychological stress perception	10 Items	(47, 48)
	Family APGAR	Family functioning	5 Items	(49, 50)
	Family Communication Scale (FCS)	Family communication	10 Items	(51, 52)
	Mindfulness Attention Awareness Scale (MAAS-5)	Mindfulness	5 Items	(53, 54)
*Parents*				
	Sociodemographics	Sociodemographic data including age, sex and gender, parental, educational/ socioeconomic status	18 Items	Standard, adapted to setting
	Parental media use	Parental media use (duration and frequency)	6 Items	(38)
	Gaming Disorder Scale for Parents (GADIS-P)	Gaming disorder according to ICD-11 criteria	10 Items	(43)
	Social Media Disorder Scale for Parents (SOMEDIS-P)	Social media disorder according to ICD-11 criteria	10 items	(55)
	Streaming Disorder Scale for Parents (STREDIS-P)	Streaming disorder according to ICD-11 criteria	10 Items	(12)
	Strength and Difficulties Questionnaire, External Assessment (SDQ-f)	Emotional and behavioral problems in children and adolescents (parental report)	25 Items	(39, 41, 42)
	Media Rules	Media rules	6 Items	(38)
	Family APGAR	Family functioning	5 Items	(49, 50)
	Family Communication Scale (FCS)	Family communication	10 Items	(51, 56)
	Patient Health Questionnaire-9 (PHQ-9)	Parental depression	9 Items	(57–59)
	Generalized Anxiety Disorder-7 (GAD-7)	General anxiety of parents	7 Items	(58, 60)
	Parenting Inventory – Revised (EEI-R)	Parenting style (without subscale about religion)	44 Items	(61)
	Questionnaire on Self-Efficacy in Parenting (FSW)	Parental self-efficacy	9 Items	(62)
	Perceived Stress Scale (PSS-10)	Psychological stress perception	10 Items	(47, 48)
	Ulm Quality of Life Inventory for Parents of Chronically Ill Children (ULQIE)	Quality of life of parents	29 Items	(63)
	Mindfulness Attention Awareness Scale (MAAS-5)	Parental mindfulness	5 Items	(53, 54)

**Table 2 tab2:** Diagram of trial activities and measurement time points.

	Study period								
	Enrollment			Intervention		Post-intervention and follow-up		Post-data collection	
Timepoint/Content	Screening (<4 weeks before baseline)	Baseline assessment (week 0)	Allocation	Res@t intervention (week 1–9 and week 15 [booster])	TAU	Post-intervention (week 10)	Follow-up (week 20)	Res@t intervention	TAU
*Enrollment*									
Eligibility screening	X								
Clinical assessment	X								
Informed consent	X								
Randomization IG/CG			X						
*Interventions*									
Intervention group (adolescent-parent dyads)				X	X				X
Waitlist control group (adolescent-parent dyads)					X			X	X
*Assessments*									
Adolescents						IG/CG	IG/CG		
Sociodemographics	X	X							
Media use	X								
GADIS-A	X					X	X		
SOMEDIS-A	X					X	X		
STREDIS-A	X					X	X		
SDQ	X					X	X		
PSQI		X				X	X		
ESS-CHAD		X				X	X		
PSS-10		X				X	X		
Family APGAR		X				X	X		
FCS		X				X	X		
MAAS-5		X				X	X		
Parents						IG/CG	IG/CG		
Sociodemographics		X							
Parental media use		X							
GADIS-P	X					X	X		
SOMEDIS-P	X					X	X		
STREDIS-P	X					X	X		
SDQ-f	X								
Media Rules		X				X	X		
Family APGAR		X				X	X		
FCS		X				X	X		
PHQ-9		X							
GAD-7		X							
EEI-R		X							
FSW		X				X	X		
PSS-10		X				X	X		
ULQIE		X				X	X		
MAAS-5		X				X	X		

GADIS-A, Gaming Disorder Scale for Adolescents; SOMEDIS-A, Social Media Disorder Scale for Adolescents; STREDIS-A, Streaming Disorder Scale for Adolescents; SDQ, Strength and Difficulties Questionnaire; PSQI, Pittsburgh Sleep Quality Index; ESS-CHAD, Epworth Sleepiness Scale - Children and Adolescents; PSS-10, Perceived Stress Scale; Family APRGAR, Family Functionality; FCS, Family Communication Scale; MAAS-5, Mindfulness Attention Awareness Scale; GADIS-P, Gaming Disorder Scale for Parents; SOMEDIS-P, Social Media Disorder Scale for Parents; STREDIS-P, Streaming Disorder Scale for Parents; SDQ-f, Strength and Difficulties Questionnaire – External Assessment; PHQ-9, Patient Health Questionnaire; GAD-7, Generalized Anxiety Disorder Questionnaire; EEI-R, Parenting Inventory - Revised; FSW, Parental Self-Efficacy; ULQIE, Ulm Quality of Life Inventory for Parents of Chronically Ill Children.

